### Setting and population

#### Study sites

In identifying potential sites for the intervention, we worked with DataRobot, Inc. to conduct a modeling exercise to estimate the likely impact of frequent self-testing on SARS-CoV-2 prevalence, incidence, and hospitalizations in cities of various geographic sizes (see Additional file 1 for the complete list of key assumptions). We assessed the impact under the following testing protocol parameters:
All household members (based on the average household size per location) take tests uniformly over 4 weeks;All household members (based on the average household size per location) take tests uniformly over 5 weeks;Two people per household test every 2 days for 4 weeks;Two people per household test every 3 days for 5 weeks;Control case in which no additional household testing was conducted.

We considered numerous community-level factors in selecting intervention sites, controlling for age distribution in each location by adjusting the model for the severity and infection fatality ratio. Specifically, the inputs (and data sources) for the model included the following:
Incidence and prevalence of SARS-CoV-2 disease (Johns Hopkins University [JHU]);Population size and density (US Census);Immunity (due to SARS-CoV-2 disease and vaccine distribution anticipated at varied dates when intervention would be conducted);Local SARS-CoV-2 reverse transcription polymerase chain reaction (PCR) testing (HHS Protect, US Department of Health & Human Services).

The DataRobot team identified 10 locations in California, Florida, Wisconsin, North Carolina, and Tennessee that optimized impact on critical outcomes, including percentage reduction in infections over the study period, the percentage reduction in incidence (i.e., new infections per capita on the final day of the study period), and percentage reduction in hospitalizations over the study period.

Following this exercise, we overlaid the results with the following information to identify preferable cities to conduct the intervention:
Availability of reliable, publicly available outcome data, including COVID-19 infections, hospitalizations, deaths, and vaccinations, as well as wastewater surveillanceOverlap with current RADx-UP sites to leverage the existing community-academic connections and infrastructure and to ensure inclusion of underserved populations;Population size requirements to maximize the impact of 2 million tests available for the intervention across the selected sites.

In consultation with state and local health departments, we selected the city of Greenville and Pitt County, NC, and the city of Chattanooga and Hamilton County, TN (40,000 test kits per site, each containing 25 tests per kit; Fig. 3) as the first sites for SYCT. We will be expanding the SYCT intervention and data collection for the ecological study to two additional communities by Fall 2021.

**Fig. 3 Fig3:**
[figure not shown]
Map of Say Yes! COVID Test intervention counties and the five groups of matched controls communities for each state, comprising the best matches for each of the following categories of matching variables: demographics (including age distribution and racial and ethnic diversity), mobility, population density, risk factors/comorbidities, socioeconomic status (including per capita income), and incidence/vaccination trajectory

We also selected multiple matched control communities for each intervention community within the same state to control state-level trends and policies **(**Fig. 3**)**. Given the limited number of counties in each state and potential confounders, no single community or composite of communities was likely to be identified as a good match in every factor affecting the outcomes. Instead, we selected five groups of matched controls for each state, comprising the best matches for each of the following categories of matching variables: demographics (including age distribution and racial and ethnic diversity), mobility, population density, risk factors/comorbidities, socioeconomic status (including per capita income), and incidence/vaccination trajectory. We chose most of the matching categories and individual variables to mirror as much as possible the National Institute of Environmental Health Sciences COVID-19 Pandemic Vulnerability Index [19]. To select control communities for the wastewater analyses, we used wastewater data availability, comparability of the sewer shed, and consistency of lab procedures as criteria.

### SYCT intervention and ecological analysis

#### Study population

The study population comprises the residents of Pitt County (encompassing Greenville), North Carolina; Chattanooga City, Hamilton County, Tennessee; and matched control communities. Community members were encouraged to participate in the SYCT intervention if they had a self-reported primary residence within one of the pre-identified communities. Individuals under 8 years of age could not participate per the at-home test indications (see below).

#### SARS-CoV-2 test

The test used for the SYCT intervention was the QuickVue SARS-CoV-2 rapid antigen assay (Quidel Corporation, San Diego, CA; Fig. 4). The test received emergency use authorization for over-the-counter distribution and at-home use by individuals aged 8 years and older from the FDA in March 2021. Individuals aged 8–14 must have an adult present to perform the test. It identifies SARS-CoV-2 nucleocapsid protein, which is generally detectable in anterior nasal specimens during the acute phase of infection. Negative tests do not definitively rule out SARS-CoV-2 infection. To conduct the test, individuals self-collect an anterior nasal swab, mix the swab in a provided tube prefilled with the testing solution, and then place a test strip into the test solution. After 10 min, the strip gives either a positive or negative result. The test strip includes an internal control – if that line is not present, the test is considered invalid (see Additional file 2). Each test kit contains supplies to perform 25 individual tests.

**Fig. 4 Fig4:**
[figure not shown]
The at-home SARS-CoV-2 antigen test used for the Say Yes! COVID Test intervention, the Quidel QuickVue At-home COVID-19 Test (Panel A). Each kit came with 25 individual tests with results shown on a lateral flow test strip. The blue line represents the control line, whereas the red line appears only if the test is positive (Panel B)

#### Test distribution

Test kit distribution began in Pitt County on April 4, 2021, and Hamilton County on May 4, 2021. All test kits were stored in Amazon warehouses located near each community. Participants could receive test kits in two ways: online orders or local distribution partners **(**Fig. 5**).**

**Fig. 5 Fig5:**
[figure not shown]
Visual representation of the two methods for distribution of Say Yes! COVID Test program test kits

##### Online order distribution:

Participants accessed the ordering website for their community through the project’s homepage, www.sayyescovidtest.org, and entered their household address information. Each order was restricted to one test kit per address. To augment participation, starting in April, individuals placing an online order could also order an extra kit for a friend. The test kits were shipped via 2-day Amazon shipping directly to the participant’s house in an Amazon box. Concurrently, the program mailed out a flyer to their address to remind them about the program’s expectations. We timed the flyer to arrive at the same time as the test kit.

##### Community distribution:

The community engagement team and project leadership formed partnerships with local distribution partners within each participating community. The local health department also served as a local distribution partner. Each distribution partner requested several test kits for distribution via the community engagement team and project leadership. These requests were sent to Amazon for fulfillment as a bulk order. Amazon shipped the bulk order test kits to the local distribution partner via 2-day shipping. Project leadership provided each local distribution partner with a corresponding number of program information flyers. Local distribution partners then held events to give away the test kits or had designated pickup times at their center or business. We listed these events and pickup times on the community’s website for the program. Participants did not have to provide any contact information. Each participant received a program information flyer at the same time as test kit pickup with instructions on how to use the test kit to participate in the at-home testing initiative.

#### Community engagement strategy

Recruitment of key stakeholders and community leaders was led by the CCPH. The team leveraged an extensive network of contacts to quickly stand up an ad-hoc advisory group of community leaders in each SYCT county to develop a community-informed strategy for distribution of at-home test kits. A series of informal listening sessions were held with the initial community advisory groups to hear their views about community interest in piloting at-home testing for SARS-CoV-2, recommendations for distribution sites, and potential barriers for rapid community-wide distribution of the at-home test kits. CCPH staff also held a half-day strategic planning session to design a comprehensive plan for disseminating information about the availability of the test kits and process for organizing community partners to serve as distribution volunteers. Upon approval of distribution plan, a site manager and staff were hired in both communities to lead recruitment and training of volunteers and promotion of the SYCT campaign.

#### Communications and micromarketing campaign

We led a public health communications and micro-marketing campaign to build widespread awareness for SYCT across the two selected communities and encourage test kit use. We first named and branded the program with local community members’ input and developed key messages and supporting materials to promote the at-home testing intervention. We established a program website and social media channels, including YouTube, Facebook, and Instagram, to drive program awareness and facilitate test kit orders and use. We also developed and disseminated various print materials, including fliers, posters, bus shelter advertisements, door hangers, and billboards, as well as television and radio ads along with online ads. Community partners received branded facemasks, promotional materials, feather flags, and distribution tents to promote local test kit distribution events. Finally, we led a public relations effort to engage national and local media outlets in sharing news of the program and information on how to participate. This strategy resulted in widespread coverage across print and digital media outlets, including CBS and NBC News features. The communications and micromarketing campaign ran through the 6-week distribution to facilitate test kit orders and continued for several weeks to remind participants to test three times a week until they used all test kits. Lessons learned in the use of communications and micromarketing to encourage awareness and uptake of at-home SARS-CoV-2 rapid tests in underserved populations will be fully described in a separate paper.

#### Testing protocol

Each participating household received one kit of 25 tests each. All test kits included an informational brochure with clear written instructions with visual aids and links to videos in English and Spanish. We instructed the participants to test one or two asymptomatic individuals within the household three times per week until all tests were used (4–5 weeks; Fig. 6). We encouraged participants to prioritize household members with the highest risk of exposure to or infection with SARS-CoV-2, such as those who worked outside the home, were not vaccinated for SARS-CoV-2, or had not been previously infected. If an individual tested positive by rapid test, we instructed them to stop testing and give their remaining tests to another household member. The SYCT program did not require positive antigen test results reporting, although, for TN participants, a phone number was available for voluntary reporting.

**Fig. 6 Fig6:**
[figure not shown]
At-home testing protocol for Say Yes! COVID Test intervention

If a participant developed any symptoms consistent with COVID-19 disease (e.g., fever, cough, shortness of breath), we recommended that the participant contact their primary physician or the local health department to obtain a PCR test for SARS-CoV-2. Reporting positive results to the health department was done through the testing institution; SYCT did not mandate result reporting. At the time of symptoms, we did not recommend additional at-home testing outside of the thrice-weekly schedule.

#### Participant support

The at-home testing kits and the marketing campaign included information about a study smartphone application and a Quick Response (QR) code to facilitate access. Developed by CareEvolution, the free app (called MyDataHelps) ran on Apple and Android devices [20]. Serving as a digital study resource, it included information about SYCT, instructions to administer at-home tests for all participants in the public health intervention, and information on how to enroll in the substudy.

#### Statistical considerations and data analysis

##### Outcomes and measures:

The data used to evaluate the impact of SYCT on participating communities will be publicly available, community-level data. The primary outcome is the number of positive SARS-CoV-2 tests per the local health department. The secondary outcomes fall into one of three categories: wastewater (e.g., SARS-CoV-2 viral copies per liter), mobility (e.g., percentage change in requests for driving directions), and other (e.g., hospitalizations attributable to SARS-CoV-2) (Table 2). We will also consider the following covariates: vaccination coverage, mobility data, and percentage of cases attributed to the B1.1.7 variant.

**Table 2 Tab2:** Summary of primary and secondary outcomes for the ecological study of the SYCT program

Outcome Measures	Endpoints	Data source	Unit of observation	Frequency of data collection	Maximum geographic granularity
Primary					
SARS-CoV-2 test results	Community prevalence point estimate and 95% confidence interval; community incidence rate	Local health departments	County	Daily	County
Secondary					
SARS-CoV-2 viral copies per liter	Community transmission	Wastewater	Wastewater treatment plant sewer shed	Twice weekly	Wastewater treatment plant sewer shed
Number of new hospitalizations for COVID-19 disease per day	Hospitalizations	Local health departments	County	Daily	Center
Hospital census	Hospital capacity/Health care utilization	Local health departments	County	Daily	County/ Healthcare center
GPS location and length of stay; requests for driving directions; requests for walking directions	Mobility	Mobile phones (Google and Apple Maps)	County	Daily	City
SARS-CoV-2-positive patients admitted to the ICU	Number of ICU admissions	Local health department	Individual	Daily	Health care Center

*Abbreviation: ICU* Intensive Care Unit

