##### Data collection procedures:

We will determine the daily case counts for ***community SARS-CoV-2 data*** using the JHU Coronavirus Resource Center for each selected county [1]. The daily case count data are made publicly available by the COVID-19 Data Repository operated by the Center for Systems Science and Engineering (CSSE) at JHU [21]. Documentation of the data by JHU is available at https://github.com/CSSEGISandData/COVID-19. This website contains a complete list of all sources used in the COVID-19 case data since January 21, 2020. There are 122 data sources for the county-level daily COVID-19 case count data. These data will be obtained through the ‘sars2pack’ R package (https://seandavi.github.io/sars2pack/) created by [name] at the University of Colorado-Anschutz and [name]. The case tracking data used for this study will include the date, count of cases, and the state and county to which the cases belong. We will obtain incidence data temporarily from the JHU source until the data resources on incident cases and other outcomes from the state health departments are successfully established.

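### The primary outcome, reported positive tests, depends on ascertainment, which the home-testing programme can itself change in either direction; the plan has no check for this

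*Protocol article*

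**What the plan says.** All references are to the Protocol article.

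**Outcome.** Outcomes and measures states: "The primary outcome is the number of positive SARS-CoV-2 tests per the local health department". Table 2 lists the endpoints for this outcome as "Community prevalence point estimate and 95% confidence interval; community incidence rate", with local health departments as the source. Data collection procedures adds "We will obtain incidence data temporarily from the JHU source", until feeds from the state health departments are in place. The case file described there holds date, count, state and county, but not the number of tests performed.

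**Home testing and reporting.** Study sites gives the supply: "40,000 test kits per site, each containing 25 tests per kit". The Testing protocol section asks for testing of household members without symptoms and says: "The SYCT program did not require positive antigen test results reporting, although, for TN participants, a phone number was available for voluntary reporting". After a positive home result: "If an individual tested positive by rapid test, we instructed them to stop testing and give their remaining tests to another household member". For participants who developed symptoms, "we recommended that the participant contact their primary physician or the local health department to obtain a PCR test for SARS-CoV-2". On how positives reach the authorities: "Reporting positive results to the health department was done through the testing institution; SYCT did not mandate result reporting".

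**Analysis.** The Analysis plan fits each outcome by community, time and their interaction, adjusted for vaccination coverage and the B1.1.7 share. It compares the interaction terms by a likelihood ratio test at alpha = 0.05. Study design names publicly reported testing data among the inputs, but no analysis of test volume or positivity is described.

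**The concern.** The Background gives the aim as finding out whether home testing reduces community transmission. A count of reported positives measures transmission only if the chance that an infection is tested and reported stays comparable between treated and control counties over time. This intervention is itself a testing programme, so it can act on that chance directly. The change would start with kit distribution, which also starts the intervention period. The time-by-community interaction would then carry any shift in ascertainment together with any effect on transmission. A real benefit could be hidden, or an apparent one created, and the primary outcome alone would not show which had happened.

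**Working it through.** **1. Scale of the programme.** 2 sites x 40,000 kits x 25 tests = 2,000,000, which reproduces the 2 million tests given in Study sites. Per site this is 40,000 x 25 = 1,000,000. That is supply, not use.

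**2. Identity.** Reported cases = infections x proportion tested and reported. Comparing treated with control, observed rate ratio = true transmission ratio x A, where A is the ratio of the ascertainment proportions. The documents give nothing from which to estimate A, so every value below is an assumption.

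**3. Downward route (home test replaces a reported test).** Let c be the share of otherwise-reported cases living in participating households, and d the share of those that go unreported. Then A = 1 - c x d. With no change in transmission, the observed ratio is:

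| c | d = 10% | d = 25% | d = 50% |
|---|---|---|---|
| 10% | 0.99 | 0.975 | 0.95 |
| 20% | 0.98 | 0.95 | 0.90 |
| 40% | 0.96 | 0.90 | 0.80 |

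**4. Upward route (home positive prompts a reported PCR).** Now let c be the share of infections in participating households, and let ascertainment there rise from a to a2. Then A = 1 - c + c x (a2/a). With a = 0.4:

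| c | a2 = 0.5 | a2 = 0.6 |
|---|---|---|
| 10% | 1.025 | 1.05 |
| 20% | 1.05 | 1.10 |
| 40% | 1.10 | 1.20 |

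**5. Reading a result back.** Suppose the observed ratio is 0.90. The true ratio is 0.90/A: 1.125 if A = 0.80, 1.00 if A = 0.90, 0.90 if A = 1.00, 0.82 if A = 1.10, and 0.75 if A = 1.20. One observed value is compatible with harm, no effect or a larger benefit.

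**6. Does the model remove A?** Vaccination coverage and variant share do not measure testing. Mobility, the other covariate listed under Outcomes and measures, does not either. The matched counties serve to control for state-level trends. They do not remove a shift that follows from a programme delivered in the treated county.

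**7. Two related points in the same outcome definition.** A count of reported positives, from people who chose or were sent to be tested, gives a rate of reported cases; it does not estimate the prevalence of infection in the community. The source also moves from local health departments (Table 2) to the JHU repository and on to state health departments. A switch within a series could add a step of its own.

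**The case against.** **The symptomatic route stays open.** Kits were for people without symptoms, and those who developed symptoms were directed to PCR, whose results are reported by the testing institution. This stands. It limits the downward route, though it does not make ascertainment equal to that in the controls: the article states no reporting or confirmatory step after a positive home test in someone without symptoms.

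**The analysis is descriptive and uses several outcomes.** Sample size and power calculation calls the analysis descriptive, and the Discussion relies on a combination of community-level outcomes. Wastewater and hospital outcomes get the same model. So the problem lies in the primary outcome read alone, not in the whole study. The descriptive label does not remove a bias, however, and the plan still tests interactions at 0.05. No rule says how the secondary outcomes qualify the primary one.

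**The 90-day post-intervention period helps.** Substitution should fade as kits run out. But a transmission effect that depends on testing would fade too, so a rebound in cases would not settle the matter.

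**Detail may sit in the SAP.** A sensitivity analysis on test volume might. The outcome, endpoints and model covariates are fixed in the article, and the point concerns those.

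**Stronger readings that the documents do not support.**
- A reader might infer that the artefact imitates success, with a fall of up to 30% (40% x 75%). Both inputs are assumptions, the figure takes no account of the PCR route, and it covers one direction only.
- A reader might infer that Tennessee phone-line reports distort that site's count and should be excluded. Nothing says they enter the case count, and the described case file could not separate them.
- A reader might infer that ascertainment changes only in treated counties. SARS-CoV-2 test notes over-the-counter authorization in March 2021, and nothing says the controls lacked home tests. A difference is plausible but unmeasured.

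**Conclusion.** The concern holds for the primary outcome as defined. Reported positives mix transmission with ascertainment, the intervention can change ascertainment in the treated county, and the stated model has no term that would show it. The direction is unknown. The size rests on assumption: with 10% to 40% of cases or infections in participating households, up to half of otherwise-reported cases there lost, or ascertainment there rising from 0.4 to as much as 0.6, the observed ratio runs from about 0.80 to 1.20 with transmission unchanged. No stated figure is wrong.

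A reader might conclude that wastewater and admissions should become co-primary. The documents do not make a good case for that. The Memphis series, the only Tennessee wastewater history described outside Chattanooga, is weekly and ends in mid-February 2021, while Tennessee study testing began on April 26, 8 days before the May 4 start in Hamilton County. From about February 15 to April 26 is some 10 weeks without stated comparison data. Admissions are likely to be sparser than cases. Re-ranking outcomes after distribution had begun, with public outcome data visible, would also be open to criticism as post hoc.

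**What to change.** Keep reported cases as the primary outcome and make four changes.

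1. Fit the Analysis plan's model to the number of reported tests and to positivity, using the testing data already named in Study design, and show both beside cases. These are diagnostics for a shift in ascertainment, not a correction for it.
2. State in advance that a change in reported cases, in either direction, is read as a change in transmission only if wastewater concentration and new COVID-19 admissions point the same way. Note the gap in the Tennessee comparison wastewater series beside that rule.
3. In Table 2, replace the community prevalence endpoint with reported cases per 100,000.
4. Take the full case series for all counties, treated and control, from one source.

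The cost is one extra public series, some edits to Table 2 and the interpretation text, and a more cautious reading of the primary outcome. If the outcomes disagree, the report will have to say that the case trend does not settle the question about transmission.
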